## Abstract

**Background:**

Evidence is accumulating that, similar to other ventral hernias, umbilical and epigastric hernias must be mesh repaired. The difficulties involved in mesh placement and in mesh-related complications could be the reason many small abdominal hernias are still primary closed. In laparoscopic repair, a mesh is placed intraperitoneally, while the most common procedure is open surgery is pre-peritoneal mesh placement. A recently developed alternative method is the so-called patch repair, in this approach a mesh can be placed intraperitoneally through open surgery. In theory, such patches are particularly suitable for small hernias due to a reduction in the required dissection. This simple procedure is described in several studies. It is still unclear whether this new approach is associated with an equal risk of recurrence and complications compared with pre-peritoneal meshes. The material of the patch is in direct contact with intra-abdominal organs, it is unknown if this leads to more complications. On the other hand, the smaller dissection in the pre-peritoneal plane may lead to a reduction in wound complications.

**Methods/Design:**

346 patients suffering from an umbilical or epigastric hernia will be included in a multi-centre patient-blinded trial, comparing mesh repair with patch repair. Randomisation will take place for the two operation techniques. The two devices investigated are a flat pre-peritoneal mesh and a Proceed Ventral Patch®. Stratification will occur per centre. Post-operative evaluation will take place after 1, 3, 12 and 24 months. The number of complications requiring treatment is the primary endpoint. Secondary endpoints are Verbal Descriptor Scale (VDS) pain score and VDS cosmetic score, operation duration, recurrence and costs. An intention to treat analysis will be performed.

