## Methods

### Design

The MORPHEUS trial is a multicentre, randomized controlled, nationwide, patient-blinded, superiority study. Patients will be randomly allocated to undergo open flat mesh repair or open patch repair for primary umbilical or epigastric hernias. The aim of this study is to determine the ideal treatment for patients with these conditions in terms of operation related complication and postoperative pain.

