### Calculation of random sample size

The primary outcome is the number of complications that require treatment. These are defined in detail further in the protocol. The occurrence of complications up to 23% is described [4]. Trials involving patch repair report a much lower complication rate, but the number of trials is significantly less. It is assumed that a conventional procedure leads to a complication in 20% of the cases [4,20]. The hypothesis is that this is reduced to 10% if a patch is used for repair. At a significance level of 5% and a power of 90%, the random sample size is 137 patients per group in a bilateral t-test. In the result analysis a Mann–Whitney parametric test will be used to evaluate a normal distribution. Therefore, the sample size must be increased by 15% [21]. Taking a minimum of 10% loss-to-follow-up into account as well, the total number of patients to be randomized becomes 346.

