### Randomisation

Sequence generation and randomisation will be performed by http://www.random.org/. The generated sequence is printed on paper cards with randomization numbers. These cards are put in non-see through envelopes. These envelopes can only be opened in the operating theatre just before timeout procedure, without informing the patient about the outcome of randomisation

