### Post-operative

Occurrence of complications and pain score at rest and pain score while exercising (VDS), the use of analgesics at that time, cosmetic (VDS) and signs of recurrence (1,3,12,24 months post-operative). The Mann–Whitney test is used for continuous data and the Pearson’s chi-square/Fisher’s exact test for categorical data. If possible a Spearman’s correlations are used for analysis of relations between the (sub) groups (comorbidity, chronic post-operative pain patients and recurrence).

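### Allocation is said to be stratified by centre, but no named test uses centre; the likely cost is a slightly conservative primary test and 0 to about 3 points of power

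*Protocol article*

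**What the plan says.** **Allocation.** The abstract (Methods/Design) states that "Stratification will occur per centre". The Design section describes the study thus: "The MORPHEUS trial is a multicentre, randomized controlled, nationwide, patient-blinded, superiority study". The number of centres is not given. The Randomisation section says only that "Sequence generation and randomisation will be performed by http://www.random.org", with the result printed on cards in opaque envelopes. It does not repeat the stratification or mention blocks or a list for each centre.

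**Analysis.** The Post-operative section, which covers the occurrence of complications, pain, cosmetic score and recurrence, commits to this: "The Mann–Whitney test is used for continuous data and the Pearson’s chi-square/Fisher’s exact test for categorical data". The Pre-operative and Per-operative sections repeat the sentence, so operation duration falls under it too. The sample-size section names a test as well: "In the result analysis a Mann–Whitney parametric test will be used to evaluate a normal distribution". The Statistical method section adds a 5% threshold, SPSS, the handling of missing values and intention to treat. No section mentions a centre term, a stratified test, a regression model or a confidence interval.

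**Endpoint and planning rates.** "The primary outcome is the number of complications that require treatment". "It is assumed that a conventional procedure leads to a complication in 20% of the cases". "The hypothesis is that this is reduced to 10% if a patch is used for repair".

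**The concern.** The analysis should reflect a factor that was used to restrict allocation. When arms are balanced within centre, differences between centres cancel out of the treatment comparison. An unstratified test still counts them in its standard error, so its p-values come out somewhat too large whenever centres differ.

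Centres could differ here. Several components of the complication definition depend partly on local practice: a stay longer than scheduled, painkillers other than paracetamol prescribed after discharge, and the frequency of wound irrigation. Operation duration may also vary by hospital.

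What is at stake is efficiency in a trial with little power to spare. The article fixes the tests by name, so this is a stated choice that does not match the stated allocation. It is not simply a detail left for an analysis plan.

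**Working it through.** **1. The plan's own figure.** For 20% versus 10%, two-sided 5%, 90% power, with mean rate 0.15:

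n per group = [1.960·√(2·0.15·0.85) + 1.282·√(0.20·0.80 + 0.10·0.90)]² / 0.10² = [0.990 + 0.641]² / 0.01 ≈ 266.

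The stated 137 per group does not reproduce; power there is 64%. The later steps do reproduce: 274 × 1.15 × 1.10 = 346.6. At 173 per group (346 in all) power is 74%. Undoing the 10% allowance, 346 / 1.10 = 314.5, so about 314 evaluable patients are used below.

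**2. Why the unstratified test is conservative.** With equal arms in equal-sized centres and no treatment effect, the Pearson test uses p̄(1 − p̄). The variance that applies is the average of p_c(1 − p_c) over centres, which is smaller by the between-centre variance of p_c. Two illustrations with two centres and mean rate 15%:

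- Rates 10% and 20%: p̄(1 − p̄) = 0.1275; within-centre average (0.09 + 0.16)/2 = 0.125; ratio 0.980. True size = P(|Z| > 1.96/√0.980) ≈ 0.048.
- Rates 5% and 25%: within-centre average (0.0475 + 0.1875)/2 = 0.1175; ratio 0.922. True size = P(|Z| > 1.96/√0.922) ≈ 0.041.

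**3. Simulation with arms balanced within centre.** From the article: rates of 20% and 10%, two-sided 5%, about 314 patients. Assumed: 5 or 10 equal centres, and normal centre effects on the log-odds with SD 0 to 1.0, calibrated so that the trial-wide rates stay at plan. There were 20,000 trials per setting. Size was computed at 15% in both arms. CMH is the Cochran-Mantel-Haenszel test by centre.

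| Centres | SD | Size, Pearson | Size, CMH | Power, Pearson | Power, CMH | Gain (points) |
|---|---|---|---|---|---|---|
| 5 | 0 | 0.052 | 0.051 | 70.0% | 69.9% | −0.1 |
| 5 | 0.3 | 0.049 | 0.049 | 70.5% | 70.7% | 0.2 |
| 5 | 0.5 | 0.050 | 0.052 | 69.7% | 70.3% | 0.7 |
| 5 | 0.8 | 0.045 | 0.051 | 70.6% | 72.3% | 1.8 |
| 5 | 1.0 | 0.042 | 0.050 | 70.7% | 73.4% | 2.8 |
| 10 | 0 | 0.049 | 0.050 | 71.3% | 71.5% | 0.1 |
| 10 | 0.3 | 0.048 | 0.049 | 71.7% | 72.1% | 0.5 |
| 10 | 0.5 | 0.047 | 0.051 | 71.2% | 72.2% | 1.0 |
| 10 | 0.8 | 0.041 | 0.048 | 71.5% | 73.8% | 2.2 |
| 10 | 1.0 | 0.040 | 0.051 | 72.5% | 75.7% | 3.3 |

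Gains were taken before rounding. Rounding to whole patients per arm made the totals 310 (5 × 62) and 320 (10 × 32), so compare along rows and not between the two blocks. The simulation error of a size is about √(0.05·0.95/20,000) = 0.0015. A separate calibrated run with 8 centres of 40 and 40,000 trials gave gains of 0.4, 0.9, 2.1 and 3.1 points at SD 0.3, 0.5, 0.8 and 1.0. In that run the Pearson size fell from 0.048 at SD 0.3 to 0.039 at SD 1.0.

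**4. What these SDs mean.** With 20% at the typical centre, log-odds −1.386 ± 1.96·SD puts 95% of centres' control rates in these ranges: 12–31% (SD 0.3), 9–40% (0.5), 5–55% (0.8) and 3–64% (1.0). The last two are wide.

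**5. Allocation without blocks.** With simple randomisation inside each centre, the Pearson test kept a size of 0.048 to 0.050 at every SD from 0 to 1.0. CMH then had lower power at SD 0 (69.3% versus 70.4%) and SD 0.3 (69.7% versus 70.3%), equal power at SD 0.5, and higher power only from SD 0.8.

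**The case against.** The strongest reply is that the matter is small and partly unproven. It has four parts.

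- **Size of effect.** Nothing in the article shows how far centres differ. Under moderate spread the gain is at most about 1 point, and the larger gains need control rates running from roughly 5% to 55%. General practitioners may also start treatment, so prescribing is not purely a hospital habit. This stands, and it limits the point to a modest one.
- **Dependence on blocking.** The conservatism needs balance within centre, and the Randomisation section describes none. Stratifying without blocks behaves like simple randomisation, and step 5 then shows a correct size for the Pearson test. This stands as a condition. An article may leave out blocking detail, but the abstract and the Randomisation section should still agree.
- **Validity.** The planned test does not exceed its 5% level in either case, so a positive result would remain sound. This stands.
- **Left to the analysis plan.** Centre adjustment is often specified there. This holds only in part, because the article already names the tests for each group of endpoints, and a later plan would have to depart from them.

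A reader might also infer that the trial's confidence intervals will be too wide. The article plans no confidence interval, so this could apply only to intervals later built to match the unadjusted tests. A reader might infer a loss nearer 4 points. One setting does give 68.1% versus 71.9%, at SD 1.0 with 8 centres. It fixes 20% and 10% at the typical centre, so the trial-wide rates rise to about 24% and 13%. At the planned rates the gain is about 3 points.

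**Conclusion.** The mismatch is real and modest. Allocation is stated to be stratified by centre, and the tests named for the primary and secondary endpoints ignore centre. If arms are balanced within centre, the unstratified test has a true size between about 0.05 and 0.04, depending on how much centres differ. It gives up 0 to 1 point of power for log-odds SD up to 0.5 and about 2 to 3 points for SD 0.8 to 1.0. If centres are alike, nothing is lost.

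These sizes rest on assumed numbers of centres (5, 8 or 10, of equal size), an assumed spread, and balance within centre that the Randomisation section does not confirm. The direction does not depend on the exact values.

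It would be wrong to read this as a risk of false-positive findings, or as the reason the trial is underpowered. The shortfall comes from the 137 per group, and adjusting for centre would not close it.

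**What to change.** 1. **Primary endpoint.** Name a Cochran-Mantel-Haenszel test stratified by centre, or logistic regression with centre, as the primary analysis. Report the Mantel-Haenszel risk difference Σw_c·d_c / Σw_c, with w_c = n_1c·n_2c / (n_1c + n_2c), and its 95% CI. Here d_c is the difference in complication proportions in centre c, and n_1c and n_2c are its arm sizes.
2. **Small centres.** State before unblinding how very small centres will be pooled.
3. **Secondary endpoints.** Use van Elteren (stratified Wilcoxon) tests or centre-adjusted models for operation duration and the VDS scores.
4. **Randomisation section.** Make it agree with the abstract: say whether there was a separate sequence for each centre and whether it was blocked. If allocation was in fact simple, correct the abstract.

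The cost is a change of wording and a little more analysis work in standard software, with no new data or patients. The one statistical downside is up to about 1 point of power if allocation is not blocked within centre and centres do not differ. The sample size needs its own correction.

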**Discussion:**

This trial is one of the first in its kind, to compare different mesh devices in a randomized controlled setting. The results will help to evaluate mesh repair for epigastric an umbilical hernia, and find a surgical method that minimizes the complication rate.

**Trial registration:**

Netherlands Trail Registration (NTR) www.trialregister.nl 2010 NTR2514 NL33995.060.10

## Background

The evidence that umbilical and epigastric hernias must be repaired using a mesh, in analogy with other hernias, is accumulating [1-7]. The use of a mesh in large hernias reduces the risk of recurrence from approximately 15-40% to 1-10% [1,4-6,8-10]. However, less research has been performed if this also applies for small hernias. To date, most small hernias are still closed with primary sutures, because of the sometimes-difficult pre-peritoneal plane in which the mesh should be placed. Therefore, the results of the Hernia Umbilicalis Mesh versus Primair suture (HUMP) trial that focuses on hernias smaller than 2 centimetres will have great added value for umbilical hernias in particular [11]. Other retrospective studies suggest that for the reoperation rate due to recurrence mesh is superior in umbilical and epigastric hernias [7]. In contrast to the HUMP trial, which places the mesh in this pre-peritoneal plane, a mesh can also be placed intraperitoneally. Advantages of intraperitoneal mesh placement can be shorter operation time. Intraperitoneal mesh placement can also be done by a laparoscopic approach [12-14]. Although in the laparoscopic mesh placement, several new fascia openings in the abdominal wall are created. The search for alternative techniques without these additional fascia defects may have played an important role in the development of these so-called patches. Patches are small devices, which can be inserted by open surgery and placed underneath the peritoneum [15-17].

In theory, such patches are particularly suitable for small hernias because of the lesser dissection necessary. It is still unclear whether this simpler procedure is also associated with at least an equal risk of recurrence and complications compared to conventional mesh placement. The ease of a surgical procedure is not a clear clinically relevant parameter, but it does often play a significant role in the surgeon’s choices. Not only are there implications for approximately 4100 umbilical and 2400 epigastric operations in the Netherlands per year [18], but also for a frequently occurring other abdominal wall hernia, the small incisional hernia.

The MORPHEUS trial is designed to clarify which treatment for primary umbilical and epigastric hernias is superior in terms of complications, costs and recurrence.

## Methods

### Design

The MORPHEUS trial is a multicentre, randomized controlled, nationwide, patient-blinded, superiority study. Patients will be randomly allocated to undergo open flat mesh repair or open patch repair for primary umbilical or epigastric hernias. The aim of this study is to determine the ideal treatment for patients with these conditions in terms of operation related complication and postoperative pain.

### Objectives/Endpoints

The primary objective of the MORPHEUS trial is to evaluate whether a ventral patch is associated with fewer complications than in conventional mesh placement for epigastric and umbilical repair. A complication is defined as an undesired development that requires treatment. Complications will be recorded up to three months after the initial procedure and pain up to 24 months post-operative. Secondary endpoints are differences in recurrence, cosmetic score, operation duration and costs.

### Participants

The institutional review board of each participating hospital has approved this randomized controlled trial. Inclusion started February the 1^st^ 2011. Adult patients with a single primary umbilical or epigastric hernia qualify for participation in the study. Patients with incarcerated hernia are also included. The maximum size of the herniation orifice can be 3 cm, corresponding with 2 fingers in analogy with the European Herniation Society (EHS) classification for inguinal hernias [19]. Patients with diagnosed ascites are excluded. This also applies for patients who cannot sufficiently understand and/or follow through participation in a trial. For the related selection criteria see Table 1.

**Table 1 T1:** Inclusion criteria

**Hernia related**	**Patient related**
In epigastric or (peri-) umbilical region	Age 18 years or older
< 3 cm (2 fingers)	Capacity (comprehension, language ability and physical ability)
Primary	No ascites
Single hernia	

Possible participants receive verbal and written information about the trial, which includes an informed consent form. Those who participate must sign the informed consent form, which must also be signed by the investigator. If a patient does not participate in the trial, the reason for this must be stated. A patient included in the trial is requested to fill in a questionnaire (P1) before the operation.

### Interventions

All procedures will take place under general anaesthesia. Administering a local anaesthetic peri-operatively is recommended. Prophylactic antibiotics are given on indication only. The use of a steri-drape as well as drains is not advised. Enlarging the herniation orifice as well as closing fascia over the mesh is permitted for both techniques.

The conventional mesh procedure begins with a para-umbilical or median incision across the hernia, then dissection of the fascia and mobilisation of the hernia sac. Opening of the hernia sac for inspection is permitted. Dissection of the pre-peritoneal area takes place after repositioning of the hernia. A flat large pore and lightweight polypropylene mesh with a minimum diameter of 6 cm is placed. Fixation of the mesh is carried out with non-absorbable monofilament sutures.

For the patch procedure, the hernia sac is opened. Possible adhesions must be released intraperitoneally. The patch is placed underneath the peritoneum, the slips fixed to the fascia. If in the surgeon’s opinion the hernia sac can be repositioned without opening it, placement is also permitted in the pre-peritoneal plane. We have chosen the standard of a PROCEED™ VENTRAL PATCH (Ethicon, Norderstedt, Germany) for this trial. No specific brand was chosen for the flat large pore and lightweight polypropylene mesh.

### Follow-up and flow chart protocol

The surgeon must fill in a questionnaire (D1) immediately after the operation. The patients are advised to take 1 gram of paracetamol 3 times a day for the first 2 weeks, and to begin mobilizing immediately according to their capacity. Follow-up at the outpatient clinic takes place after 1 and 12 months, with the practitioner filling in the questionnaires (D2 and D3). The patients are asked to fill in a questionnaire 3 and 24 months after the operation (P2 and P3). These questionnaires will be sent to the patients by postal service or e-mail. Non-responders were contacted up to three times by means of a telephone questionnaire. Figure 1 shows the studies flow-chart.

**Figure 1 F1:**
[figure not shown]
Trial flow-chart.

### Calculation of random sample size

The primary outcome is the number of complications that require treatment. These are defined in detail further in the protocol. The occurrence of complications up to 23% is described [4]. Trials involving patch repair report a much lower complication rate, but the number of trials is significantly less. It is assumed that a conventional procedure leads to a complication in 20% of the cases [4,20]. The hypothesis is that this is reduced to 10% if a patch is used for repair. At a significance level of 5% and a power of 90%, the random sample size is 137 patients per group in a bilateral t-test. In the result analysis a Mann–Whitney parametric test will be used to evaluate a normal distribution. Therefore, the sample size must be increased by 15% [21]. Taking a minimum of 10% loss-to-follow-up into account as well, the total number of patients to be randomized becomes 346.

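### 137 per group gives about 64–65% power for 20% versus 10%, not 90%; the 346 randomised give about 74–75% if all are analysed and about 70% after the planned 10% loss

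*Protocol article*

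**What the plan says.** All inputs stand in one paragraph of the protocol article, under Calculation of random sample size.

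- Control rate: "It is assumed that a conventional procedure leads to a complication in 20% of the cases".
- Patch rate: "The hypothesis is that this is reduced to 10% if a patch is used for repair".
- Error rates, sidedness and result: "At a significance level of 5% and a power of 90%, the random sample size is 137 patients per group in a bilateral t-test".

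The paragraph then adds 15% because a Mann–Whitney test is to be used, allows for at least 10% loss to follow-up, and concludes that "the total number of patients to be randomized becomes 346". The abstract (Methods/Design) repeats this total: "346 patients suffering from an umbilical or epigastric hernia will be included".

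The Design section calls the trial a superiority study. The Post-operative part of the statistical section assigns the Mann–Whitney test to continuous data and Pearson's chi-square or Fisher's exact test to categorical data.

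**The concern.** This paragraph is the only power justification given for the primary endpoint. It states every input needed to check it, and 137 per group is about half of what a standard two-group calculation gives for those inputs. Since 346 is built directly on 137, the shortfall carries into the final trial size.

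At stake is how a negative result can be interpreted. As written, the trial has a 10% chance of missing a true halving of complications. With the planned loss that chance is about 30% (about 35% with Fisher's exact test), and with no loss about 25%.

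**Working it through.** **Inputs (Calculation of random sample size).** p1 = 0.20, p2 = 0.10, difference 0.10, two-sided α = 0.05 (z = 1.960), power 0.90 (z = 1.2816). Allocation of 1:1 is implied by the equal group size.

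**1. The plan's own figures.** The step from 137 to 346 can be followed: 2 × 137 = 274; 274 × 1.15 = 315.1; 315.1 × 1.10 = 346.6, given as 346. The 137 itself is not reproduced by any standard two-sample calculation tried (steps 2 and 3).

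**2. Sample size for 90% power.** The pooled two-proportion formula, with mean rate 0.15, is

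n = [1.960 × √(2 × 0.15 × 0.85) + 1.2816 × √(0.20 × 0.80 + 0.10 × 0.90)]² / 0.10²
= [1.960 × 0.5050 + 1.2816 × 0.5000]² / 0.01
= (0.9898 + 0.6408)² / 0.01 = 265.9, so **266 per group**.

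Other two-sided 90% versions agree:

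| Method | n per group |
|---|---|
| Unpooled proportions | 263 |
| Arcsine | 261 |
| Two means, SD √0.125 to √0.1275 | 263–268 |
| Continuity-corrected | 286 |

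**3. Relaxed settings.** One-sided 5% with 90% power gives 217, two-sided 5% with 80% power gives 199, and one-sided 5% with 80% power gives 157. None reaches 137.

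**4. Power at the sizes in the plan.** By normal approximation, power = Φ[(0.10 × √n − 0.9898) / 0.5000].

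- n = 137: (1.1705 − 0.9898) / 0.5 = 0.361, power 64.1%
- n = 156: (1.2490 − 0.9898) / 0.5 = 0.518, power 69.8%
- n = 173: (1.3153 − 0.9898) / 0.5 = 0.651, power 74.3%

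Here 173 is 346 / 2, and 156 is 346 × 0.90 / 2 = 155.7, rounded. Exact enumeration of the two binomial distributions gives:

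| Per arm | Situation | Pearson chi-square | Fisher exact |
|---|---|---|---|
| 137 | stated base size | 64.9% | 58.9% |
| 156 | 346 less 10% loss | 70.2% | 64.8% |
| 173 | all 346 analysed | 75.2% | 70.4% |

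A two-sided t-test, the test named in the paragraph, gives 64.5%, 70.2% and 74.6% for the same three sizes. The choice of test therefore does not explain the gap.

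**5. What 346 can detect, and what 90% would need.** With 156 per arm, 20% versus 7.5% has 89.7% power by normal approximation and 90.7% by exact chi-square. For 20% versus 10% at 90% power, 2 × 266 = 532 evaluable patients are needed; 532 / 0.90 = 591.1, so 592 randomised in two equal arms.

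**The case against.** **The 15% and 10% additions bring the trial above 137 per group, so 137 alone understates it.** This is true, and the correct figures for the trial are those at 156 and 173 per arm. Even the best case, with no loss, is about 15 points below 90%. A reader might take 70% as the power of the full 346; it holds only after the planned loss.

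**The 15% may be legitimate.** A reader might infer that it has no basis at all. The documents do not support so firm a statement. The endpoint is called a number of complications, and for a per-patient count a rank test would not be equivalent to a chi-square test. The cited source for the 15% is also not at hand. However, the inputs are proportions of cases with a complication, which points to a yes/no outcome, and the statistical section gives such data to chi-square or Fisher. On that reading the 15% does not match the planned test. In either case it adds patients, so it does not cause the shortfall.

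**Where 137 came from.** One-sample formulas land near it: comparing 10% with a fixed 20%, two-sided, gives [(1.960 × 0.4 + 1.2816 × 0.3) / 0.1]² = 136.5. A reader might conclude that a one-sample or one-sided calculation was used. The protocol does not say so, a one-sided origin would contradict its two-sided wording, and the conclusion does not depend on the origin.

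**Loss to follow-up.** Multiplying by 1.10 instead of dividing by 0.90 gives 346 rather than 350 (315.1 / 0.90 = 350.1). This is a minor note beside a shortfall of 592 − 346 = 246 randomised patients.

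**Misreading of a null result.** The protocol does not plan to read a non-significant result as equality. The point is only that its stated power would lend such a reading unearned support.

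**Conclusion.** The sample-size statement is wrong as written. Under the protocol's own assumptions, 137 per group gives about 64–65% power, and 90% power needs about 266 evaluable per group. The 346 to be randomised give about 74–75% if all are analysed and about 70% after the planned 10% loss (about 65% with Fisher's exact test).

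These figures assume a yes/no endpoint per patient, equal allocation, a two-sided 5% test, and true rates of 20% and 10%. The conclusion is firm: every standard two-sample method tried gives at least 261 per group at two-sided 90%. It does not extend to how 137 was obtained, nor to a claim that the trial must be enlarged.

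**What to change.** Keep 346 and correct the paragraph under Calculation of random sample size:

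- State that 346 randomised, about 156 evaluable per arm after 10% loss, give about 70% power for 20% versus 10% with a two-sided 5% chi-square test (about 65% with Fisher's exact test), and about 74–75% with no loss.
- State that 90% power after 10% loss is reached only for about 20% versus 7.5% (chi-square), and that 90% power for 20% versus 10% would need about 266 evaluable per group, or about 592 randomised.
- If the endpoint is yes/no per patient, as the inputs imply, name the chi-square/Fisher test of the Post-operative section as the basis, and remove the t-test and Mann–Whitney wording together with the 15% step. If a count per patient is meant, say so and base the calculation on counts.
- As a minor correction, compute loss as n / 0.90.

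The cost is a change of wording and a less favourable stated power. No extra patients are needed to make the statement correct. Enlarging the trial to reach 90% would be a separate decision.

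### The primary test is misdescribed, the endpoint shifts between a count and a yes/no rate, and the 15% sample-size increase has no basis for a yes/no rate

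*Protocol article*

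**What the plan says.** **Endpoint.** The abstract (Methods/Design) states "The number of complications requiring treatment is the primary endpoint". The section Calculation of random sample size repeats it: "The primary outcome is the number of complications that require treatment". The assumptions that follow are per-patient rates: "It is assumed that a conventional procedure leads to a complication in 20% of the cases", and "The hypothesis is that this is reduced to 10% if a patch is used for repair". The Post-operative section lists the occurrence of complications. The Definitions section lists five kinds of qualifying complication within 3 months and does not say whether a patient can count more than once.

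**Test.** The size comes from a t-test: "At a significance level of 5% and a power of 90%, the random sample size is 137 patients per group in a bilateral t-test". The next sentence is "In the result analysis a Mann–Whitney parametric test will be used to evaluate a normal distribution", and the 15% increase is drawn from it. The Post-operative section gives a general rule: "The Mann–Whitney test is used for continuous data and the Pearson’s chi-square/Fisher’s exact test for categorical data". The Statistical method section sets the 0.05 threshold and names no test for the primary endpoint.

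**The concern.** There are two faults.

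First, the sentence that announces the analysis is wrong in both its claims. Mann–Whitney is not parametric, and it compares two groups rather than evaluating a distribution. A design figure, the 15%, rests on that sentence. Such an allowance is meant to cover a rank test replacing a t-test on a measured variable. It has no role when the outcome is complication yes or no.

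Second, the unit of the primary endpoint is not settled. If it is a number per patient, the data-type rule points most naturally to Mann–Whitney. If it is whether a patient had a complication, the rule points to chi-square or Fisher. These are different outcomes, not just different tests: a patient with three complications weighs more than a patient with one under the first reading and the same under the second. If this stays open, the choice could be made after the results are seen. Only the second reading matches the 20% versus 10% hypothesis.

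**Working it through.** **Inputs.** From Calculation of random sample size: 20% and 10%, two-sided 5%, power 90%, 137 per group, +15%, 10% loss, total 346. Equal allocation is an assumption, implied by a single per-group figure.

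**1. How 346 arises, and what the 15% contributes.**
- 137 × 1.15 = 157.55 per group.
- 157.55 × 1.10 × 2 = 346.6, stated as 346. The last steps reproduce.
- Without the 15%: 137 × 1.10 × 2 = 301.4.
- The 15% step therefore accounts for 346.6 − 301.4 = about 45 patients.

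**2. Does the choice of test matter on a yes/no outcome?** Let a and b be the numbers of patients with a complication, n the patients per arm, N = 2n and t = a + b.
- Pearson: X² = N(a − b)² / [t(N − t)].
- Mann–Whitney with tie correction and no continuity correction: z² = X² × (N − 1)/N.
- Evaluable patients: 346/2 = 173 per arm; 173 × 0.9 = 155.7, about 156. So N = 312 and the factor is 311/312 = 0.997.
- Example near the assumed rates, a = 31 and b = 16: X² = 312 × 15² / (47 × 265) = 70,200 / 12,455 = 5.64; z² = 5.64 × 0.997 = 5.62. Both exceed 3.84.
- Exact power by enumerating both binomials at 156 per arm: Pearson 70.2%, Mann–Whitney 70.2%.

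The two tests are practically the same test here. A 15% allowance for moving to Mann–Whitney therefore buys nothing for this endpoint.

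**3. Power of the planned size under the chi-square test.**
- Normal approximation: z = [0.10 × √156 − 1.960 × √(2 × 0.15 × 0.85)] / √(0.2 × 0.8 + 0.1 × 0.9) = (1.249 − 0.990) / 0.5 = 0.52, so power is about 70%. This agrees with the enumeration.
- Size for 90% power: n = (1.960 × 0.505 + 1.282 × 0.5)² / 0.10² = 266 per group. With 10% loss, 266 / 0.9 = 296 per group, or 592 in total.
- The stated 137 was not reproduced by pooled, unpooled, arcsine, continuity-corrected or t-test formulas, one- or two-sided, at 80%, 85% or 90% power.

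The gap between 90% and 70% comes from the base figure of 137, not from the choice of test.

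**4. Count or proportion, side by side.**

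| Place | Wording points to |
|---|---|
| Abstract, Methods/Design | number of complications |
| Sample size, first sentence | number of complications |
| Sample size, assumptions | share of patients |
| Post-operative | occurrence, with the test set by data type |

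The documents give no distribution of complications per patient, so the effect of choosing a count cannot be calculated from them.

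**The case against.** The strongest defence is that the intention is readable. The assumed rates, the reference to occurrence, and the term complication rate in the Discussion all point to a proportion of patients, for which the data-type rule gives chi-square or Fisher. On that outcome Mann–Whitney would give nearly the same p-value. This stands, and it limits the harm. It does not rescue the sentence in the sample-size section or the 15% built on it, and it does not remove the count wording in two places.

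Three stronger readings are tempting and are not supported:
- *A reader might infer that a chi-square on pooled complications would treat dependent events as independent.* No section proposes that analysis. Mann–Whitney on per-patient counts would keep the patient as the unit. Any figure for the inflation needs an assumed number of items per patient, which the article does not give. Nor is it clear that one abscess would count several times, since a complication is defined as a development that requires treatment.
- *A reader might infer that leaving Pearson and Fisher open costs power, since exact power at 156 per arm is 70.2% and 64.8%.* The pair is normally read as Fisher for small expected counts. Here the expected number under no difference is 156 × 0.15 = about 23 complicated patients per arm, so Pearson would apply. The selection rule is also the kind of detail left to an analysis plan.
- *A reader might hold the absence of a risk difference against Mann–Whitney.* A chi-square test gives none either, and the estimate can be specified elsewhere.

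**Conclusion.** The point holds in limited form. The Mann–Whitney sentence is wrong as written, the 15% has no basis for a yes/no endpoint, and the article does not settle whether the primary comparison is of counts or of proportions. The 15% accounts for about 45 of the 346 patients. It does not follow that the decisive test would give a wrong answer: on a yes/no outcome the two candidate tests agree almost exactly.

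The planned 346 gives about 70% power for 20% versus 10% with a chi-square test, assuming 1:1 allocation and 10% loss. That shortfall from 90% is a separate fault in the base size of 137. Correcting the test will not repair it, but it has to be stated once the sample-size paragraph is rewritten.

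**What to change.** 1. Define the primary endpoint as the proportion of patients with at least one complication, as listed in Definitions, within 3 months. Use that wording in the abstract, the sample-size section and the Post-operative section.
2. Name one primary test, two-sided at 5%: Pearson chi-square, or Mantel–Haenszel by centre because randomisation is stratified per centre. Report the risk difference with its 95% confidence interval.
3. Delete the Mann–Whitney sentence and the 15% step.
4. Restate the sample-size justification, since removing that step takes away part of the stated basis for 346. Give the power of 346 under the named test: about 70% at about 156 evaluable patients per arm.
5. Report the number of complications per patient descriptively.

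The cost is small: a revised sample-size paragraph, matching endpoint wording, and a less favourable stated power. No new data collection is needed.
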